## Introduction

There is progress towards attaining the third Sustainable Development Goal (SDG) of under-five (U5) mortality of 25 per 1000 live births by 2030, in India. Neonatal mortality rate is the most important contributing factor of the U5 mortality.^1 2^ Further decline in neonatal mortality may require newer interventions for prevention or treatment of neonatal infections like meningitis, pneumonia, septicaemia that result in more than a quarter of the 1 million neonatal deaths every year in India.^2^

The ProSPoNS trial^3^ proposes to evaluate the role of probiotics in prevention of neonatal infections (sepsis) among the vulnerable group of low-birth weight infants contributing the highest rates of morbidity and mortality. A larger sample size and precise outcome measures differentiate this trial from the earlier conducted pilot study that showcased a 21% non-significant decline in morbidity due to neonatal sepsis in the intervention arm. Considering the 30% prevalence of low-birth weight (LBW) in India and 30% mortality due to neonatal sepsis, even a small decline in the incidence of sepsis would translate to a large number of new born lives saved.^3^

If the intervention is proven to be efficacious, it would be important to know whether it is also a cost-effective intervention. There are few examples in the literature where economic evaluations have been conducted on other effective interventions to prevent neonatal sepsis.^4 5^ It cannot be overemphasised that along with clinical effectiveness of interventions, an estimate of economic effectiveness either in terms of costs or utilities (disability-adjusted life years; DALYs and Quality adjusted life years; QALYs) is required to make correct choices about their inclusion in public health programmes. This is of immense importance in presence of multiple competitive options where prioritisation is needed.

Ranjeva *et al*^6^ have quantified the scope of the public health and economic burden of neonatal sepsis in Sub-Saharan Africa. However, evidence on the health economics aspect of neonatal sepsis prevention effect of probiotics has not been ascertained so far. We propose to evaluate the cost utility of probiotic intervention for prevention of neonatal sepsis within the ProSPoNS trial.

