## Background

ProSPoNS trial is a phase III multicentre randomised, double-blind placebo-controlled trial, being conducted at six study sites across India. It is a global Health trial funded by the UK Research and Innovation.

The Study is ongoing at six sites across India: Jawaharlal Institute of Postgraduate Medical Education and Research (JIPMER), Puducherry, Mahatma Gandhi Institute of Medical Sciences (MGIMS), Wardha, King Edward Memorial Hospital (KEM Hospital), Pune, Asian Institute of Public Health (AIPH), Bhubaneswar (with recruitments from SCB Medical College and Hospital, Cuttack), Subharti Medical College (SMC) and Lala Lajpat Rai Memorial Medical (LLRM) College District women hospital, Meerut and Lady Hardinge Medical College (LHMC), Kalawati Saran Children’s Hospital (KSCH), Delhi. The primary objective is to estimate a 30% reduction in the incidence of neonatal sepsis in the intervention arm with daily supplementation of 1 mL (10 billion CFU/mL) of Vivomixx drops over a period of 30 days in 0–2-month-old LBW infants. 6144 low-birth weight (between 1500 g and 2500 g) infants would be recruited to the study from the six study sites located in Bhubaneswar, Meerut, New Delhi, Puducherry, Pune and Sewagram, between ages 3 and 7 days of life.

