### Theory of change

More than one-third of the estimated four million neonatal deaths around the world each year are caused by severe infections, and a quarter—around one million deaths—is due to neonatal sepsis/pneumonia alone. Panigrahi *et al* in their study which was conducted in the year 2017 reported that the Culture-confirmed incidence of sepsis as 6.7/1000 births with 51% Gram negatives (Klebsiella predominating) and 26% Gram positives (mostly Staphylococcus aureus). The SDG for child survival cannot be achieved without substantial reductions in infection-specific neonatal mortality.^1^ Due to non-specific signs and symptoms, sepsis is difficult to diagnose. The chances of recovery and survival depend on the correct diagnosis, referral, reaching a facility and adequate treatment by appropriately trained health workers and high-quality services.

Low-birth weight is one of the important indirect causes of deaths in neonates accounting for 40%–80% of neonatal deaths worldwide.^2^ LBW neonates are immune compromised and manifest poor cognitive functions.^7^ Since LBW infants are more prone to infections, neonatal mortality and morbidity may be decreased by preventing neonatal infection.

Antibiotic therapy is the mainstay of current therapeutic management of neonatal infections. For serious infections in new borns and young infants, there is a lack of guidelines on rational antibiotic use.^8^ In the absence of rapid diagnostics, non-judicious use of antibiotics contributes to the rising antimicrobial resistance. Antibiotic overuse is linked with disturbing the gut ecosystem. The problem of drug resistance outweighs the fast pace of newer generation antibiotic production.

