A health economic evaluation using CUA design will be conducted within the ProSPoNS trial. The results would provide the incremental costs and health gains of the probiotic intervention in absence of any prevention modality being implemented or available. Decision-analytical modelling using the trial results would be extrapolated to the target population and time horizon to inform policy on the potential for incremental costs offsets attributable to prevention of morbidity with the proposed intervention. The CUA will use the present results as cost per case of neonatal sepsis prevented. CUA will present the results as cost per DALY averted. Intervention costs and effects will be extrapolated to the Indian neonatal population. Modelling will be used for the target population, time horizon and the decision context to provide much required information for the policymakers. It would guide further decision for upscaling the intervention, if it is found to be efficacious. If the incremental costs of the intervention can be offset by the gains in terms of effectiveness (ie, DALYs), it may be presented for induction within the ambit of existing governmental programme. Modelled CUA results can be presented as health-adjusted life years saved and savings of the healthcare system by disease prevention. We will calculate the incremental cost-effectiveness ratios as the difference in the costs between the intervention and the comparator divided by the difference in health outcomes.

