### Study details

Total of 6144 (N) new born babies with LBW would be screened for eligibility and randomly assigned to probiotic (n=3072) or placebo (n=3072) groups and administered 1 mL of the probiotic suspension daily for 30 days. The study would use Interactive Web Respons System (IWRS) for the purpose of stratified randomisation by birth weight, sex and study site. Trained field workers will make home visits daily for first 7 days and thereafter three times in a week till day 30 of the follow-up period to ensure and monitor adherence to the intervention and collect morbidity information. After the 30-day intervention period, home visitation will continue at weekly interval till day 60 of life. During home visitation as per schedule, trained fieldworkers would screen infants for symptoms/signs of possible serious bacterial infection (PSBI)/clinical illness/clinical severe infection. To record the adverse event (AE)/serious adverse event (SAE) (if any), continuous monitoring and reporting of ongoing medical conditions, signs and symptoms will be conducted by field worker during their scheduled follow-up home visits using software on handheld device during the 2-month period of follow-up. Presence of any danger signs would be evaluated, and need for referral would be assessed: if a child is found to have any symptoms/signs from the list, the field worker will accompany the infant to facility for examination by study physician (referral). The study physician would examine the infant again for symptoms/signs of PSBI/clinical illness/clinical severe infection and confirm the diagnosis. Investigations such as blood culture, sepsis screen would be performed for suspected cases of neonatal sepsis by study physician. If required, the infant would be hospitalised for treatment. Data on outcomes, lab investigation and treatment during clinical management of the sick, new born will be collected and SAEs will be reported as per regulatory guidelines. Blood culture isolates will be shipped by site to microbiology lab at All India Institute of Medical Sciences, New Delhi for quality assurance purpose.

The study will be implemented according to MRC guidelines for management of global health trials and will be governed by a Trial Steering Committee and a Data Management Committee.

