#### Uncertainty analysis

Both deterministic and probabilistic sensitivity analysis (PSA) will be undertaken to address the effect of uncertainties present in analysis. For PSA, all the parameter values will be varied within a plausible range. Based on nature of parameter, an appropriate probabilistic distribution will be assigned such as beta distribution for risk and utility parameters, gamma distribution for cost parameters, uniform distribution for demographic parameters, etc. The results under PSA will be simulated 999 times to report a 95% CI for ICERs.

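### 999 PSA draws leave avoidable seed error in the upper 95% limit of the ICER: about -15% to +22% if the trial has roughly 80% power, other values under other assumptions

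*Protocol article*

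**What the plan says.** The Uncertainty analysis section of the protocol article commits to a number of draws and to the summary they serve: "The results under PSA will be simulated 999 times to report a 95% CI for ICERs". It names families of input distributions, "beta distribution for risk and utility parameters, gamma distribution for cost parameters, uniform distribution for demographic parameters, etc", without their parameters, and gives no reason for choosing 999.

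The Outcome measures section defines the ICER as a ratio: "the difference in the costs between the intervention and the comparator divided by the difference in health outcomes". Table 2 makes incremental cost per DALY averted the objective, and the text after that table says that the analysis is done in MS-Excel.

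**The concern.** A 95% interval read from 999 draws has 2.5% of 999, about 25 draws, beyond each limit. For a quantity with a roughly normal distribution that is adequate. The ICER is different: a draw in which few DALYs are averted has a small denominator and a very large ratio, so the upper tail is long and thinly populated, and the 97.5th percentile is estimated where draws are sparse.

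Two analysts running the same model on the same data with different seeds could then report visibly different upper limits. That difference carries no information about the intervention, and more draws reduce it.

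**Working it through.** The figure 999 is a choice with no derivation, so there is nothing to reproduce. The check asks how far the upper limit moves between seeds.

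**Inputs from the article**
- Draws: 999, for a 95% interval of the ICER (Uncertainty analysis).
- Arm sizes: "randomly assigned to probiotic (n=3072) or placebo (n=3072) groups" (Study details).
- Target effect, relative risk 0.70: "The primary objective is to estimate a 30% reduction in the incidence of neonatal sepsis in the intervention arm" (Background).
- Smaller effect, relative risk 0.79: "21% non-significant decline in morbidity due to neonatal sepsis in the intervention arm" (Introduction).
- Case fatality, for illustration: "30% mortality due to neonatal sepsis" (Introduction).

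**Inputs that had to be assumed**
- Baseline sepsis risk. The only incidence quoted, "Culture-confirmed incidence of sepsis as 6.7/1000 births" (Theory of change), comes from a cited study and is not a design input of this trial. Risks of 3% to 10% were scanned.
- Intervention cost of 500 or 2000 rupees, treatment cost of 2003 to 30,000 rupees, cost CV of 0.1 to 0.4, and 27 DALYs per death.
- The interval is the percentile interval of the simulated ratios, and the effect is taken from this trial alone.

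**Step 1: link baseline risk to power.** With p the control risk and RR the relative risk, effect/SE = p(1-RR) / sqrt{[p(1-p) + pRR(1-pRR)]/3072}. At p = 0.0463 and RR = 0.70 this is 0.01389/0.00496 = 2.80, and 2.80 - 1.96 = 0.84, which is 80% power. At p = 0.0612 it is 0.01836/0.00566 = 3.24, which is 90% power.

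**Step 2: analytic benchmark.** The SE of an estimated percentile is sqrt[q(1-q)/n]/f, where f is the density at that percentile. For a normal variable at 97.5% with n = 999 it is sqrt(0.025 × 0.975/999)/0.0584 = 0.00494/0.0584 = 0.085 SD. If the ICER were lognormal, the 95% seed range would be 1.96 × 0.085 × log-SD: about ±3% at log-SD 0.2, ±8% at 0.5 and ±17% at 1.0. The error therefore grows with the skewness of the ICER.

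**Step 3: repeated PSA.** Arm risks were drawn from beta distributions with 3072 per arm, case fatality from a beta and costs from gammas. The whole PSA was repeated over many seeds. The table gives the central 95% range of the upper limit across seeds, relative to its median.

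| Baseline risk | Relative risk | 999 draws |
|---|---|---|
| 10% | 0.70 | -10% / +13% |
| 4.6% (80% power) | 0.70 | -15% / +22% |
| 3% | 0.70 | -21% / +33% |
| 4.75% | 0.79 | -23% / +39% |

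At 10,000 draws the 80% power row falls to about -4% / +6%. A second set of runs with other assumed inputs gave -8% / +9%, -14% / +20%, -21% / +30% and -23% / +39% for the four rows. It gave -11% / +14% at 6.1% risk (90% power). At 4.6% risk it gave -5% / +6% with 10,000 draws and about ±1.5% with 100,000. Within that set the ranges barely changed with the cost inputs, or when a lognormal relative risk replaced the beta arm risks.

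**Step 4: rate of improvement.** Error falls with 1/sqrt(n), and sqrt(10,000/999) = 3.16, in line with the threefold reduction seen.

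**Step 5: scale.** At 4.6% risk, one cost set gave a median ICER of about 16,800 rupees per DALY averted and an interval of about 7,000 to 60,000. A seed range of -14% / +20% puts the reported upper limit between 60,000 × 0.86 = 51,600 and 60,000 × 1.20 = 72,000. The interval itself spans more than eightfold (60,000/7,000 = 8.6).

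**The case against.** The strongest reply is that nothing here is wrong or contradicted. About 1000 draws is not an error, and the seed, convergence check and statement of Monte Carlo error are details that an article may leave to the full protocol or analysis plan. That is right about those details, and their absence is not part of this point. The number 999 is different, because the article states it.

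A second reply is that the size is not a property of the plan, since it rests on a baseline risk and PSA spreads that the article does not give. This stands. A reader might infer that 999 draws always mean a 15-20% shift, but that holds only near 80% power for a 30% reduction. The shift is smaller with higher power and larger with a smaller effect or a rarer outcome.

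Three further inferences are tempting and unsupported:
- *More draws would remove the error at no cost.* They shrink it, and the run time in MS-Excel has not been tested.
- *The error is as large for any PSA summary.* A probability of cost-effectiveness from 999 draws has a Monte Carlo SE of at most sqrt(0.25/999) = 1.6 percentage points. The large figures belong to a percentile of a ratio.
- *Seed noise could reverse a funding decision.* The article states no willingness-to-pay threshold and does not make the upper limit the quantity to be judged, so no changed conclusion can be shown.

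Finally, more draws do not cure a percentile interval of a ratio when some draws have DALYs averted near or below zero. With effect/SE = 2.80 about 0.25% of draws fall below zero, and the share rises as the effect shrinks. More draws then estimate precisely a limit that is itself hard to interpret. This limits what the change can achieve.

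**Conclusion.** The point holds as a minor improvement in precision. The stated 999 draws leave seed error in the upper limit of about -15% / +22% if the trial has roughly 80% power for a 30% reduction. Across the other scenarios in the table it runs from about -10% / +13% to about -23% / +39%. These figures assume a percentile interval, an effect taken from this trial alone, and baseline risks that the article does not give. Seed error is much smaller than the parameter uncertainty that the interval is meant to show. The trial design and data are unaffected.

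**What to change.** In the Uncertainty analysis section, replace 999 with at least 10,000 draws. In the 80% power case this brings the seed range of the upper limit to about -4% / +6%. If the workbook allows 100,000, the range is about ±1.5%. Fixing and reporting the seed alongside would be sensible, but does not itself reduce the error.

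The cost is a longer run in MS-Excel. No data collection, sample size or model structure changes.

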#### Budget impact analysis

A budget impact analysis is proposed to be conducted to estimate the financial consequences of increasing uptake of probiotic supplementation for LBW infants in the neonatal care under NHM, over the near future (3 to 5 years). Data regarding the target population of LBW infants will be available by extrapolating the data from the RCT, as will be other epidemiological inputs to populate the budget-impact model. At present, there are no alternative prevention modalities for neonatal sepsis present (other than hand hygiene and exclusive breastfeeding). Therefore, assumption would be made regarding the uptake of probiotic supplementation (based on the results of the study).

#### Stakeholder analysis

A range of potential stakeholders will be consulted, involving experts such as neonatologists/paediatricians, academics, policymakers, programme managers, industry, patient group representatives, etc. Multiple consultations with stakeholders will be done during the conduct of study as well as dissemination of study results.

## Patient and public involvement

Patients or caregivers or members of public were not involved in the development of this protocol.

## Discussion

The ProSPoNS trial is evaluating the role of probiotics intervention in prevention of neonatal infections, a major cause for neonatal mortality. To date, no prevention modalities other than hand hygiene and exclusive breast feeding have been successfully incorporated in programmes for prevention of neonatal infections. Panigrahi *et al* established benefit of *Lactobacillus planitarum* with fructooligosaccharides intervention in prevention of sepsis and related deaths in new borns; however, the study did not assess the cost-effectiveness of the intervention. There is no study in the literature evaluating the cost-effectiveness of this novel disease prevention technology. We have proposed such evaluation alongside the ProSPoNS trial.

An RCT design, considered a gold standard for such evaluations, is being used in the trial. However, there are disadvantages of using RCT data quoted in the literature. Data from a single RCT may not be adequate for estimation of cost utility as RCTs mainly focus on a single intervention and have small follow-up period, thus, lack to provide evidence on effectiveness of multiple alternatives and situations beyond the trial conditions. The treatment effect measured in a single study may be relevant for a particular setting but has limited generalisability of results in populations other than the one studied.^17–19^ We propose using a modelling approach to overcome the above-mentioned shortcomings of RCT data.

There are a few examples of estimation of cost-effectiveness of disease preventive technologies in the neonatal population. A study conducted in Sub-Saharan Africa estimated that neonatal sepsis resulted in 5.29–8.73 DALYs lost annually accounting for an economic burden from $10 billion to $469 billion (per annum). It was recommended that a strategic plan for the treatment and prevention of neonatal sepsis may reduce this burden.^6^ A cost-effective analysis conducted in Ghana reported that alcohol-based hand rub (ABH) effectively reduced the patient cost of neonatal bloodstream infection (BSI), hospital cost associated with BSI, length of hospital stay and deaths due to BSI by 41.7%, 48.5%, 50% and 73%, respectively. It was also estimated that ABH reduced the incidence of hospital-acquired neonatal infections by 16%.^4^ Current study would estimate the cost-effectiveness of a novel neonatal sepsis prevention modality.

In considering cost-effectiveness, measures on treatment effect over longer time horizon than RCTs are often required. Therefore, we have proposed a modelling approach in addition to the use of primary data coming from the ongoing RCT. This approach would use and provide a wider range of assumptions/parameters from multiple data sources and evaluate the long-term utility of the probiotic intervention in disease prevention.

Expected outcomes of study and policy implications: the health economic evaluation would generate data on cost involved with the new intervention as compared with the control arm with uncertainty range, incremental costs and health outcomes for both study arms with uncertainty range, ICER, sensitivity and threshold analyses. It would be helpful for the policymaker to understand the cost utility of the probiotic intervention in the presence of other competing priorities.

### Strengths

This would be the first study evaluating cost-effectiveness of using probiotic intervention among low-birth weight newborn infants in India.This study would inform incremental costs per DALY averted with use of probiotics, which will be key for prioritising resource allocation in view of other competing demands for child health; therefore, crucial for public policy decisions.Data from the RCT would be complimented with the use of a model-based approach to explore scenarios beyond the trial data.

### Challenges

Generalisability and external validity of findings from economic evaluation concurrently performed with the main study may not represent the same treatment effects and costs as in routine clinical practice.

### Registration

The protocol has been approved by the regulatory authority (Central Drugs Standards Control Organisation; CDSCO) in India (CT-NOC No. CT/NOC/17/2019 dated 01 March 2019). The ProSPoNS trial is registered at the Clinical Trial Registry of India (CTRI). Registered on 16 May 2019

### Ethics and dissemination

Approval has been obtained from EC of each of the six participating sites (MGIMS Wardha, KEM Pune, JIPMER Puducherry, AIPH, Bhubaneswar, LHMC New Delhi, SMC Meerut) as well as from the ERC of LSTM, UK. A peer-reviewed article will be published after completion of the study. Findings will be disseminated in the community of the study sites, with academic bodies and policymakers.
